**Objectives:**

1. To test the hypotheses that greater changes in CVD risk factors, CVD risk score and CVD risk management follow the NHS Health Check than are observed in control participants;
2. To test the hypothesis that all-cause mortality and the incidence of clinical events (new diagnoses of ischaemic heart disease, stroke, diabetes mellitus and chronic kidney disease) may be lower in participants who received NHS Health Checks than control participants;
3. To test the hypothesis that inequalities in the outcomes of Health Checks across deprivation category may be lower in NHS Health Check participants than in control participants.
4. **Background**

Cardiovascular disease is the leading cause of death worldwide and in the United Kingdom (1). Almost 155,000 deaths annually are caused by CVD in UK, accounting for more than a quarter of all deaths (2). Diabetes also is increasing in frequency, with four million people in UK living with diabetes, which is associated with serious complications leading to disability and premature mortality (3).The NHS Health Check (NHSHC) is a primary prevention programme that was introduced in England. The programme targets individuals aged 40 to 74 years, who have not yet developed CVD and are not treated for elevated risk, and estimates their risk of heart disease, stroke, type 2 diabetes, chronic kidney diseases and some forms of dementia (4). After identifying individuals at elevated risk, a personalised risk management intervention is provided. This programme provides an opportunity in terms of addressing multiple risk factors which, if successful, might reduce the risk of several diseases. Results from the Department of Health economic model suggested that the NHS Health Check could save 650 lives, and 1600 heart attacks and 4000 cases of diabetes could be prevented a year (5).

Since the implementation of the NHS Health Check, studies have examined the effectiveness of the programme in terms of CVD risk reduction. Cochrane, Davey (6) monitored the changes in CVD risk factors after the first year of implementing the NHSHC and assessed the benefit of the lifestyle support component of the programme. They compared participants who received the health check alone with participants who received the health check together with additional lifestyle change support. The mean CVD risk declined in both groups. In the health check group, it was 32.9% at baseline and it reduced to 29.4% (p<0.001) after one year follow up. In the health check plus lifestyle support group CVD risk was 31.9% at baseline and it reduced to 29.2% (p<0.001) after one year follow up (6). Another study aimed at assessing the CVD risk reduction after one year follow-up (7). In participants who had a completed health check (n=1886) the mean global CVD risk score was reduced significantly from 28.2% (CI= 27.3,29.1) to 26.2% (CI= 25.4, 27.1)(7). Both studies showed modest reduction in CVD risk and CVD risk factors. However, participants were only followed after one year. Since the NHSHC was introduced in 2009, long term follow up would provide further assessment of the programme’s effectiveness, which this study aims to achieve.

The present analysis will draw upon our previous CPRD study on health checks (Protocol: 13_071A). (8) The previous study constructed a matched cohort design in which participants who had received health checks between 1 April 2010 and 31 March 2013 and who had at least 12 months records, were compared with controls who did not receive a health check. This previous study focused on risk factor detection and showed that health checks are associated with increased detection of hypercholesterolaemia, and to a lesser extent obesity and hypertension, but smokers may be under-represented among participants in the programme. The proposed study aims to evaluate longer term follow-up of substantive health outcomes. This study aims, therefore, to evaluate changes in risk factors, clinical events and mortality outcomes. In this proposed study, all individuals will have the potential to provide a minimum of three years of follow-up following the health check.

1. **Study Type**

The study will be hypothesis testing, estimating health check programme through a comparison of health check and control participants.

1. **Study Design**

Matched cohort study in the Clinical Practice Research Datalink (CPRD), including participants who received the NHSHC with matched control participants. This design will enable a comparison of health outcomes between participants who had the health check with control participants who attend the same general practice but did not attend the NHSHC programme.

1. **Sample Size**

Based on Forster et al. study (8) (ISAC protocol 13-071A), we intend that this study will include the same 75,123 participants with a record of a complete NHSHC between 1st of April 2010 and 31st of March 2013 with follow-up data available three years after their health check (up to 31/3/2016), and the same 182,245 matched control participants who did not receive the check. All individuals were eligible for data linkage as discussed in section H.

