Primary outcomes: Data will be analysed for changes in all-cause mortality and CHD and stroke clinical events, diabetes diagnosis and chronic kidney disease (CKD) diagnosis. The Read codes used to identify cases of CHD in CPRD data will be those listed in reference 9. The Read codes used to identify cases of stroke in CPRD data will be those listed in reference 10. (9, 10) , while ICD-10 codes will be used in HES data. Where feasible stroke will be classified as haemorrhagic or ischaemic. CHD events will be classified as angina, myocardial infarction, coronary artery bypass surgery or percutaneous coronary intervention and other. To identify cases of diabetes, diabetes drug prescriptions will be analysed by mapping drug codes to chapter subheadings in the British National Formulary (6.1 for drugs used in diabetes). Medical diagnosis codes and levels of HbA1c levels (6.5%) will be analysed as well to identify diabetes diagnosis. Medical diagnosis codes and levels of serum creatinine will be used to identify CKD cases. (11) . Details of proposed case definitions are given in Table 1.

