**Table 1: Case definitions for key measures:**

| **Condition** | **Read Codes** | **Therapy Codes** | **Test results** | **ICD-10 codes** |
| --- | --- | --- | --- | --- |
|  |  |  |  |  |
| **Ischaemic heart disease** | As listed in reference 9. | N/A | N/A | I20-I25 |
|  |  |  |  |  |
| **Stroke** | As listed in reference 10. | N/A | N/A | I60-I64 |
|  |  |  |  |  |
| **Diabetes mellitus** | As listed in Appendix 1. | BNF chapter 6.1.1 and 6.1.2 | HbA1c >=6.5% (48 mmol/mol) | E10-E14 |
|  |  |  |  |  |
| **Chronic kidney disease** | K05 and K06 codes | N/A | eGFR based on serum creatinine using CKD-EPI equation (11) | N18, N19 |
|  |  |  |  |  |

Secondary outcomes: CVD risk and CVD risk factors, including: smoking, BP, total cholesterol, HDL and BMI. Data on medication prescription for antihypertensive drugs, lipid-lowering drugs, antiplatelet drugs and nicotine replacement therapy will be analysed by recording drug codes to chapter subheadings in the British National Formulary (chapter 2 for CVD drugs).

1. **Data/ Statistical analysis**

The proportion of participants with values recorded for five risk factors (blood pressure, total cholesterol, HDL, BMI and smoking status) will be evaluated. Risk factor values will also be assessed. Changes over time in prescription of drugs for CVD risk management, including antihypertensive, lipid-lowering, antiplatelet and nicotine replacement therapy, will be evaluated.

The association between NHSHC and changes in CHD, stroke, diabetes and CKD clinical events will be examined using Cox hazard and Poisson regression models. Person-time approach will be adopted, where the start date is the date of the check. Hazard ratios will be estimated using Cox proportional hazards models and incident rate ratio using Poisson regression model. The proportional hazard assumptions will be tested. Linear mixed models will be used to study changes in continues outcomes (BP, cholesterol and BMI measurements). Follow-up will be censored if a control participant receives a health check at a later date. The effect of deprivation will be evaluated. Potential effect modification from deprivation category will be evaluated by testing for an interaction of health check status and deprivation category.

1. **Plan for addressing confounding**

To control for potential cofounders, model covariates will include age, gender, ethnicity and deprivation indices.

1. **Plan for addressing missing data**

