Recording of risk factor values is an outcome of importance in respect of evaluating NHS health checks. Prescriptions, clinical events and deaths that are not recorded will be presumed to be absent, because recording of these measures is expected to be complete.

1. **Limitations of the study design, data sources and analytical methods**

A randomised evaluation would provide the optimal study design but as health checks are part of a national policy, the present non-randomised design will offer an achievable study design. We expect a high level of completeness for recording of NHS health checks because use of mandated Read codes is used for reimbursement of practices. We acknowledge that there may be lack of standardisation of blood pressure measurements and recording of measures such as smoking and body mass index may be subject to misclassification. Use of diagnostic codes for CVD events varies between general practices and some clinical events are recorded with codes that lack precision.

1. **Patient or user group involvement (if applicable)**

Patients have not contributed to the development of this protocol but we have engaged with patients in our health check evaluation work and will be able to discuss the results of this study with patient groups.

1. **Plans for disseminating and communicating study results, including the presence or absence of any restrictions on the extent and timing of publication**

The results of this study will be reported in national public health events and we will also prepare peer review paper for publication. It will also contribute to a PhD thesis.

1. **References**

| Medcode | ReadCode | ReadTerm | Type |
| --- | --- | --- | --- |
| 506 | C100112 | Non-insulin dependent diabetes mellitus | 2 |
| 608 | 66A2.00 | Follow-up diabetic assessment | 2 |
| 711 | C10..00 | Diabetes mellitus | 2 |
| 758 | C10F.00 | Type 2 diabetes mellitus | 2 |
| 1038 | C100011 | Insulin dependent diabetes mellitus | 1 |
| 1323 | F420.00 | Diabetic retinopathy | 2 |
| 1407 | C10FJ00 | Insulin treated Type 2 diabetes mellitus | 2 |
| 1549 | C10E.00 | Type 1 diabetes mellitus | 1 |
| 1647 | C108.00 | Insulin dependent diabetes mellitus | 1 |
| 1682 | C101.00 | Diabetes mellitus with ketoacidosis | 1 |
| 1684 | 66A4.00 | Diabetic on oral treatment | 2 |
| 2340 | F381311 | Diabetic amyotrophy | 2 |
| 2342 | F372.12 | Diabetic neuropathy | 2 |
| 2378 | 66AJ.00 | Diabetic - poor control | 2 |

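### For diabetes and CKD, the overall Cox and Poisson ratios mix detection at the check with prevention and are biased upward, so they should not serve as the test of lower incidence

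*Protocol*

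**What the plan says.** - **Hypothesis.** Objective 2 reads, in part, "new diagnoses of ischaemic heart disease, stroke, diabetes mellitus and chronic kidney disease) may be lower in participants who received NHS Health Checks".
- **Primary outcomes.** Under Exposures, Outcomes and Covariates these are "changes in all-cause mortality and CHD and stroke clinical events, diabetes diagnosis and chronic kidney disease (CKD) diagnosis". Table 1 allows diabetes to be identified from an HbA1c result at or above 6.5% and CKD from an eGFR derived from serum creatinine, alongside diagnosis codes and, for diabetes, drug codes.
- **Time zero and models.** Data/Statistical analysis says "Person-time approach will be adopted, where the start date is the date of the check" and that "changes in CHD, stroke, diabetes and CKD clinical events will be examined using Cox hazard and Poisson regression models". Proportional hazards will be tested. No lag, landmark or separate treatment of diagnoses made at the check is described.
- **Controls checked later.** "Follow-up will be censored if a control participant receives a health check at a later date".
- **Unrecorded events.** Plan for addressing missing data says "clinical events and deaths that are not recorded will be presumed to be absent, because recording of these measures is expected to be complete". The rule covers both groups.
- **Baseline exclusions.** Study Population lists earlier diabetes, coronary heart disease, stroke, and treatment with antihypertensives or statins. CKD is not on the list.
- **What the check does.** The Lay Summary and Background name type 2 diabetes and chronic kidney disease among its targets. Background also reports that the team's earlier study found checks associated with more detection of hypercholesterolaemia and, less strongly, of obesity and hypertension.
- **Limitations.** These cover measurement standardisation, misclassification and imprecise codes, but not unequal testing between the groups.

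**The concern.** A case definition that uses a test result can be met by that route only in someone who is tested. If the check prompts HbA1c or creatinine testing, attenders are tested at time zero and controls only when usual care happens to test them. Diabetes or CKD that was present but unrecognised on the start date would then appear in the checked group as a cluster of early events. The same disease in an untested control would be scored as absent.

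This error runs in one direction: it raises the ratio for attenders. Once those cases have been found, the checked group has less undiagnosed disease left to find, so the ratio would tend to fall with time. One overall hazard ratio or rate ratio averages these two phases, and its value depends partly on length of follow-up.

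At stake is the reading of two of the five primary outcomes. A programme that truly lowers diabetes or CKD incidence could show a ratio of 1 or more and be reported as ineffective or even harmful.

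**Working it through.** **1. The plan's own figure.** Sample power calculation covers CHD only: 3 per 1,000 per year, 75,000 checked, 182,000 controls, risk ratio 0.85, three years, alpha 0.05 (taken as two-sided), power above 90%.
- Three-year risks: control 0.003 × 3 = 0.009; checked 0.85 × 0.009 = 0.00765.
- Two-proportion power: 92.7%.
- Events: 75,000 × 0.00765 + 182,000 × 0.009 = 574 + 1,638 = 2,212. Schoenfeld power at a hazard ratio of 0.85: 93.5%.

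The figure reproduces and is not in dispute. It provides the ratio of 0.85 used below as a benchmark. The protocol gives no incidence or undiagnosed prevalence for diabetes or CKD, so those inputs are assumptions.

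**2. Break-even.** Let *i* be the yearly rate of recorded diagnosis in controls and *e* the net extra proportion of attenders diagnosed over three years because of the check, after allowing for catch-up.

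Observed ratio = (0.85 × 3*i* + *e*) / 3*i*. This equals 1 when *e* = 0.15 × 3*i*.

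| Assumed *i* per 1,000 per year | *e* | Attenders, of 75,123 |
|---|---|---|
| 3 | 0.135% | 101 |
| 4 | 0.18% | 135 |
| 6 | 0.27% | 203 |
| 8 | 0.36% | 270 |

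**3. Allowing for depletion and catch-up.** Let *u* be undiagnosed prevalence at the start, *s* the share of it found at the check, *c* the yearly rate at which it is found anyway, and *a* = 1 − exp(−3*c*).

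Checked risk = 0.85 × (3*i* − *u* × *a*) + *u* × [*s* + (1 − *s*) × *a*]; control risk = 3*i*.

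Example with *i* = 0.006, *u* = 1%, *s* = 0.5, *c* = 0.1, so *a* = 0.259:
- Checked: 0.85 × (0.018 − 0.00259) + 0.01 × (0.5 + 0.5 × 0.259) = 0.0131 + 0.0063 = 0.0194.
- Ratio: 0.0194 / 0.018 = 1.08, although the true ratio is 0.85.

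With *i* = 4, 6 or 8 per 1,000, *u* = 0.5%, 1% or 2%, *s* = 0.25, 0.5 or 0.8 and *c* = 0.1 or 0.2 (54 combinations), a true 0.85 appears as 0.89 to 1.90. It exceeds 1 in 35 of the 54.

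**4. Available follow-up.** Data run to 31/3/2016. Every check up to 31/3/2013 can therefore reach three years, but only checks up to 31/3/2011 can reach five. Linked HES and ONS data end on 30/09/15, so in the linked analysis three years is reachable only for checks up to 30/09/2012.

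**The case against.** The strongest reply is that the mechanism is inferred. The protocol never says that the check measures HbA1c or creatinine. It says that the check estimates risk, and the five risk factors in its analysis section are blood pressure, total cholesterol, HDL, BMI and smoking. The team's previous CPRD study reported more detection of other risk factors, not of diabetes or CKD. This stands as a limit on certainty. The inference is still a reasonable one from the check's stated targets, the test-based case definitions and the results of that CPRD study.

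Second, the proportional-hazards test may reveal the problem, and what follows a failed test is commonly left to a statistical analysis plan. That is fair. However, the direction of the hypothesis, the start date, the case definitions and the presumption of complete recording are all fixed in the protocol.

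Third, Background cites a model in which the programme prevents 4,000 diabetes cases a year, so a prevention hypothesis for diabetes is legitimate. This also stands. Removing it is one option, not a necessity.

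Some stronger readings are tempting but not supported:
- *The ratios measure detection instead of prevention.* They mix the two. Some scenarios above leave the ratio below 1, and a ratio clearly below 1 would still be informative.
- *The presumed-absent rule disadvantages one group.* It covers both. The bias comes from unequal testing.
- *Detection at a control's later check is dropped.* The protocol says that follow-up is censored, but not how a diagnosis dated that day is counted.
- *Cases found at the check add to a full later incidence.* At an assumed 5 per 1,000 per year, 75,123 × 0.005 × 3 = 1,127 cases. Another 1% (751) would give 1 + 751 / 1,127 = 1.67. Unless the 1% is net of later catch-up, this counts some people twice.

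**Conclusion.** The concern holds in a limited form. For diabetes and CKD, the planned overall ratios combine detection with prevention and are biased upward if, as is likely, attenders are tested at the start and controls are not. A null or raised ratio could then not be taken as evidence against prevention.

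Little extra detection is needed: a net 0.14% to 0.36% of attenders cancels a true ratio of 0.85, for assumed control rates of 3 to 8 per 1,000 per year. These sizes rest wholly on assumed rates and serve as illustration.

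CKD has an added weakness. Objective 2 speaks of new diagnoses, so removal of earlier CKD may be intended, but the listed exclusions do not include it. All-cause mortality, myocardial infarction and stroke are much less affected, and the CHD power statement is untouched.

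**What to change.** - For diabetes and CKD, report ratios separately for 0 to 12 months and beyond 12 months, or use a lagged or landmark analysis. Show cumulative incidence by group at 1 and 3 years, and at 5 years only for checks up to 31/3/2011. Apply the earlier data cut-off in the linked analysis.
- Do not use the overall ratio for these two outcomes as the test of lower incidence. Describe it as detection plus prevention, and state that neither period alone isolates prevention.
- Exclude CKD recorded before the start date, in both groups.
- Keep mortality, CHD and stroke as the outcomes for the lower-incidence test. Within CHD, show myocardial infarction and revascularisation separately from angina, using the planned classification.
- Add differential ascertainment to the limitations.

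The cost is some protocol wording, one further exclusion and a re-run of models already planned. The price in interpretation is a weaker effectiveness claim for two outcomes.

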**Sample power calculation:**

Assuming that the background incidence of CHD is about 3 per 1,000 per year and the type 1 error rate is set at 0.05, if there are 75,000 health check participants and 182,000 control participants, there will be more than 90% power to detect a risk ratio of 0.85, for reduction of CHD incidence, over three years of follow-up.

1. **Data Linkage Required (if applicable)**

We have requested linkage to the Index of Multiple Deprivation data to test whether the outcomes of the NHS Health Checks differ across different socioeconomic status. We already have deprivation data obtained for protocol 13_071A but we will request all linked data again from the latest linkage Set (i.e. Set 12). This will ensure that we are working with the most accurate and consistent data (e.g. if a patient's postcode has been added or changed).

In addition, we are requesting ONS mortality data to enable cause of death analysis. We also plan to use integrated HES data to evaluate hospital admissions with ischaemic heart disease or stroke events. We are aware that a small number of patients may be eligible for linkage to IMD data but not eligible for linkage to the ONS mortality and inpatient HES data. This is because eligibility for linkage to IMD depends on the availability of a valid postcode, whereas eligibility for linkage to ONS and HES data depends on availability of a valid NHS number.

We will initially conduct the analysis using CPRD data only (the ‘unlinked analysis’). Subsequently, we will conduct a similar analysis using CPRD data together with linked data (the ‘linked analysis’). We will take into account the coverage period for the ONS mortality and inpatient HES data. Set 12 linkages provide ONS mortality and inpatient HES data through to 30/09/15, so the time period for the linked analysis will be restricted in comparison to the unlinked analysis. Patients who are not eligible for ONS and HES linkage will be excluded from the linked data analysis by restricting the study population to those eligible for all linkages. The loss of participants should not be large because the initial sample was drawn from linkage eligible participants.

1. **Study Population**

The original sample was extracted from the October 2014 release of CPRD for 140,356 participants with a record of an NHS Health Check between 1 April 2010 and 31 March 2013, from 452 general practices in England. We restricted the sample to all 106,784 participants registered with 334 general practices with IMD 2010 quintile for England, linked via the participant postcode, at the lower super-output area level. We also excluded all patients who were ever treated with antihypertensive drugs (8531) or statins (1529) before the date of the check. We also excluded patients (4859) who did not have a full year of up to standard record before the date of the check and one patient whose check was after 31 March 2013. We also excluded patients with diabetes (227), coronary heart disease (2) or stroke (3) diagnosed before the check. There remained 91,618 participants who had a health check between 1 April 2010 and 31 March 2013, who had at least 12 months record, were never treated with antihypertensive drugs or statins, and were not diagnosed with diabetes, stroke or CHD before the check. For these 91,618 participants, eligible control participants were identified for 75,123 (82%) and these participants, and their matched controls, will be included in the present study.

1. **Selection of comparison group(s) or controls**

Control participants were selected if they were eligible for the NHS Health Checks but did not receive the check, they might have been invited to attend the Health Check, or not. The control participants were individually matched by general practice, gender and age with participants who received the Health Check.

1. **Exposures, Outcomes and Covariates**

Primary outcomes: Data will be analysed for changes in all-cause mortality and CHD and stroke clinical events, diabetes diagnosis and chronic kidney disease (CKD) diagnosis. The Read codes used to identify cases of CHD in CPRD data will be those listed in reference 9. The Read codes used to identify cases of stroke in CPRD data will be those listed in reference 10. (9, 10) , while ICD-10 codes will be used in HES data. Where feasible stroke will be classified as haemorrhagic or ischaemic. CHD events will be classified as angina, myocardial infarction, coronary artery bypass surgery or percutaneous coronary intervention and other. To identify cases of diabetes, diabetes drug prescriptions will be analysed by mapping drug codes to chapter subheadings in the British National Formulary (6.1 for drugs used in diabetes). Medical diagnosis codes and levels of HbA1c levels (6.5%) will be analysed as well to identify diabetes diagnosis. Medical diagnosis codes and levels of serum creatinine will be used to identify CKD cases. (11) . Details of proposed case definitions are given in Table 1.

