A new programme of NHS Health Checks (NHSHC) was introduced in the UK in 2009. This aims to provide cardiovascular risk assessment every five years for adults aged 40-74 who are not already diagnosed with CVD or diabetes. The NHSHC offers a promising strategy for preventing CVD, yet several concerns have been raised in relation to its uptake, cost-effectiveness, success in reducing diseases and effectiveness of risk management. In this context, evaluation of the programme’s longer-term outcomes is crucial. This study aims at evaluating changes in risk and cardiovascular clinical events and mortality outcomes following uptake of a health check. We will use a matched cohort design in the CPRD by comparing participants with a record of a complete NHSHC between 1st of April 2010 and 31st of March 2013 with follow-up data available for a minimum of three years after their health check up to 31st March 2016, together with matched control participants who did not receive a health check. We will adopt a time-to-event framework with date of check as the start date to evaluate the onset of new prescriptions. Hazard ratios will be estimated using the cox proportional hazards model and incident rate ratios using Poisson regression to examine the association between the programme and changes in clinical events and mortality.

1. **Objectives, Specific Aims and Rationale**

**Aim:** To measure the long term outcomes of the NHS Health Checks programme and evaluate whether outcomes following an NHS Health Check are more favourable than in controls.

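### The one-year prior-record rule is stated for health-check attenders but not for the reused controls, so unless the earlier study applied it to both, old disease and continuing prescriptions can count as new in controls

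*Protocol*

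**What the plan says.** The Study Population section lists the exclusions made among people with a health-check record, including: "We also excluded patients (4859) who did not have a full year of up to standard record before the date of the check". It then repeats the condition for those left: "There remained 91,618 participants who had a health check between 1 April 2010 and 31 March 2013, who had at least 12 months record". The Background section, summarising the earlier study, also places the condition on the health-check group, "who had at least 12 months records, were compared with controls who did not receive a health check".

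For controls, the section on selection of comparison groups says: "Control participants were selected if they were eligible for the NHS Health Checks but did not receive the check", whether or not they had been invited. It adds: "The control participants were individually matched by general practice, gender and age with participants who received the Health Check". It gives no length of record or registration, and registration date is not a matching factor.

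Programme eligibility is described in the Technical Summary as "adults aged 40-74 who are not already diagnosed with CVD or diabetes". The Background adds that people must not be under treatment for elevated risk. Neither mentions length of record.

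On analysis, the protocol says: "Person-time approach will be adopted, where the start date is the date of the check". Controls have no check, and no start date is stated for them. Objective 2 concerns new diagnoses of ischaemic heart disease, stroke, diabetes and CKD. The Technical Summary adds the onset of new prescriptions. Events and prescriptions that are not recorded are presumed absent, and the covariates are age, gender, ethnicity and deprivation.

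**The concern.** A minimum period of prior record lets existing disease and treatment reach the file before someone is declared free of them. Someone who joined a practice shortly before the start date may look disease-free and untreated only because the history has not been entered. If it is entered later and dated at entry, it passes the baseline exclusion and is then counted as a new event.

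If the rule operates in both arms, this problem is reduced in both. If it operates only among attenders, prevalent disease is added to control incidence alone, and the check looks protective for CHD, stroke, diabetes and CKD even if it does nothing. For drug initiation the direction reverses: a new registrant's continuing prescription looks like a start, so control initiation rises and any increase after a check is understated. None of the planned covariates measures time since registration, so adjustment would not remove either effect.

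**Working it through.** **The plan's own figure.** The power statement uses CHD incidence of 3 per 1,000 per year, three years, 75,000 attenders, 182,000 controls, ratio 0.85 and type 1 error 0.05. Three-year risks are 0.003 × 3 = 0.009 in controls and 0.85 × 0.009 = 0.00765 in attenders. Expected events are 182,000 × 0.009 = 1,638 and 75,000 × 0.00765 = 573.75. Two-sided power is 92.7% by two proportions, 93.5% by Schoenfeld's formula and 91.8% by a Wald test on the log rate ratio. The claim of more than 90% reproduces and is not in dispute.

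**How large a filter the rule was among attenders.** Taking the exclusions in the order listed, 106,784 − 8,531 − 1,529 = 96,724 remained after the drug exclusions, and 4,859 / 96,724 = 5.0%. If the order differed, the share would be close to this (4,859 / 106,784 = 4.6%).

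**Does programme eligibility imply a year of record?** The stated criteria are age, existing disease and treatment. The 4,859 people had a health check recorded without a full year of up-to-standard record, so being treated as eligible did not require it.

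**What one-sided use of the rule could do to CHD (illustration).** Let f be the share of controls with under a year of record, and q the share of those whose old CHD is entered after the start date and counted. Neither is in the documents. With a true ratio of 1.00, the apparent ratio is

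1 / (1 + f × q / 0.009).

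With 182,245 controls, expected CHD events are 182,245 × 0.009 = 1,640. Borrowing the attender share, f = 5.0% is about 9,155 controls.

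| q | False control events at f = 5.0% | Apparent ratio, f = 1% | f = 5.0% | f = 10% |
|---|---|---|---|---|
| 0.5% | 46 | 0.99 | 0.97 | 0.95 |
| 1% | 92 | 0.99 | 0.95 | 0.90 |
| 2% | 183 | 0.98 | 0.90 | 0.82 |

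**Break-even.** With the power section's figures, reading 0.85 when the truth is 1.00 needs 1,638 × (1 / 0.85 − 1) = 289 false events. That is 289 / 182,000 = 0.16% of controls, or q = 3.2% at f = 5.0%.

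**The case against.** The strongest reply is that an unstated criterion is not an unapplied one. The controls are not being chosen here: Sample Size says the same 182,245 people will be used, and the full selection rules belong to protocol 13_071A, which is not at hand. A reader might infer that short-record controls were definitely admitted and that the CHD comparison is therefore biased. The documents do not support that inference. Study Population also says that eligible controls were found for only 75,123 of 91,618 attenders (82%), leaving 91,618 − 75,123 = 16,495 without one. That hints at a stricter definition of an eligible control, though it does not show that record length was part of it.

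The mechanism also has conditions. History entered with its original date falls before the start date and is not incident, and the protocol does not say how late-entered history is dated. A new registrant already prescribed a statin or antihypertensive would be screened out if the treatment condition was applied to controls. Lacking a full year of up-to-standard record is not necessarily the same as being newly registered.

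The sizes are assumed. The 5% share is borrowed from attenders, and nothing supports the 0.5% to 2%. The nearest figures are small: of the 96,724 − 4,859 − 1 = 91,864 attenders left after the drug, record and date exclusions, only 2 were removed for prior CHD and 3 for prior stroke. Those are people whose history was already on file after a year of record, so they do not measure q, but they lend no support to its upper values.

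Finally, the linked analysis uses hospital admissions, which are not created when a practice enters old history, so comparing linked and unlinked results gives a partial check.

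All of this limits what can be claimed. It does not remove the asymmetry in the text: the section that defines controls gives no record condition, and programme eligibility does not supply one.

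**Conclusion.** The point holds conditionally. As written, the one-year rule binds attenders and not controls. If the earlier study did not apply it to controls, GP-recorded CHD, stroke, diabetes and CKD comparisons would be biased in favour of the check and drug-initiation comparisons against it. All-cause mortality is not affected by this mechanism, and hospital admissions in the linked analysis are largely unaffected.

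The size cannot be derived from the documents. The range of about 0.97 to 0.90 for a null CHD ratio rests on three assumptions: 5% of controls have a short record, 0.5% to 2% of those have old CHD entered late, and that history is dated at entry. It shows that the issue could matter beside a target of 0.85. It is not an estimate of bias in this study. The point deserves correction because the cohort is already built, the conclusion turns on one unstated fact, and the check is cheap.

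**What to change.** In the section on selection of comparison groups, define each control's start date as the matched attender's check date. Verify that at that date every control had at least one full year of up-to-standard record, no earlier antihypertensive or statin, and no earlier diabetes, CHD or stroke. Drop controls who fail, and any attender left without a control, and restate the numbers under Sample Size. If the earlier study already applied these conditions to controls, say so in one sentence; no numbers then change.

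The cost is one filter on the existing cohort and possibly a small share of controls. There are 182,245 / 75,123 = 2.4 controls per attender. If 5% of controls were lost and no attenders, with 0.009 × 75,123 = 676 CHD events in attenders under no effect, the standard error of the log rate ratio would go from √(1/676 + 1/1,640) = 0.0457 to √(1/676 + 1/1,558) = 0.0461, a rise of about 1%.
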